#### Population of case-matched general population controls

For each case, two individuals of the same sex as the case will be selected from the general population who were registered in the same National Health Applications and Infrastructure Services (NHAIS) system as the case at the case's date of *index diagnosis*, were alive at the case’s date of *index diagnosis*, were born within 1 month either side of the case’s date of birth, and had had their first invitation to bowel screening in the same year as the case. If no matched control is found for a particular case with a date of birth within 1 month either side of the case's date of birth, the range will be expanded to 3 months either side (or 6 months either side if the case’s age at *index diagnosis* of primary CRC is over 75). For subsequent phases of this evaluation (main phase onwards), they will not have been included as population controls in previous evaluation periods.

Incident advanced stage cases and matched general population controls will be selected a posteriori by the PRU according to various designs as described in Table 1. In the initial stages of the evaluation, incident cases will be restricted to those individuals with Duke’s stage B or worse primary CRC at *index diagnosis* (Designs 1–3). Data permitting, we will also include individuals diagnosed with a Duke's stage A primary CRC during the study window but who were subsequently found to develop metastases (i.e. the cancer becomes stage B or worse) in order to avoid introducing a bias *in favour* of screening by excluding them from the population of cases and underestimating the proportion of Duke B+ tumours among screen-detected. Indeed, metastases are more likely to be early and therefore minimal and so missed in screen-detected compared to symptomatic cases; as a consequence, a minority of screen-detected tumours may be classified as having a less advanced stage leading to the underestimation of screening exposure in cases, and creating a bias *in favour* of screening.

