### Data sources & collection

Recently diagnosed cases will be obtained from the Northern and Yorkshire Cancer Registry and Information Service (NYCRIS) which is the lead registry for colorectal cancer. This cancer registry has linked the NHS BCSP data to the National Cancer Data Repository (NCDR) up until 2010 and is planning to update this linkage on a regular basis. Matching general population controls will be retrieved from the Health & Social Care Information Centre (HSCIC) database at Exeter. Tumour pathology variables will be obtained from the NCDR, including Dukes’ stage of disease at diagnosis which is the only currently nationally available staging variable. Detailed pathology information is also available via the NHS BCSP [8]. Bowel cancer, cervical and breast screening variables will be obtained from the HSCIC.

The data will be checked and cleaned by the PRU Senior Data Manager, transferred to separate Oracle tables, and stored on a UNIX server kept in a secure server room within the Wolfson Institute of Preventive Medicine. Access to the Oracle database is from PCs on the Queen Mary University of London secure network using SQLNET.

All data will be processed in accordance with NHS Information Governance guidelines (NHS IG Toolkit, https://www.igt.hscic.gov.uk/).

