### Power calculation

For the main phase of the study, all cases complying with the selection criteria in the whole of England covering the 2-year evaluation period will be collected. We anticipate biennial accrual of thousands of CRC cases (e.g. 33,218 - 18,590 male and 14,628 female cases - in 2010 [19]), for which statistical power will not be an issue and for which there will be considerable precision.

For the pilot phase of the study, the sample size was estimated to enable sufficient power to answer the primary objective with relative confidence.

Nakajima and collaborators [22] found that the odds ratio of developing advanced stage CRC for those screened within 2 years before the diagnosis versus those not screened using a FIT was 0.76 (95% CI 0.45 – 1.28) when both interval and screen-detected cancers were included in the analysis. We will therefore assume an odds ratio of 0.8 as FIT has been reported to have a higher sensitivity compared to gFOBt (reviewed in [2]).

We anticipate 64% agreement of exposure for matched cases and controls. We further anticipate 55% exposure for cases, 59% for controls. This would imply that for 39% of case–control pairs, both case and control would have been exposed to screening, for 25%, neither would have been exposed, for 16%, the case would have been exposed and not the control, and for 20% the control would have been exposed and not the case (illustrated in Table 3). This would give the expected odds ratio of 0.8. To have 90% power to detect this odds ratio as significant would require 259 discordant pairs and therefore 719 cases with one control per case [26]. As we propose to have two controls per case, 719 cases for the pilot study is considerably more than is strictly needed as the number of potential discordant pairs will be substantially increased.

**Table 3 Tab3:** **Power calculation assumptions around exposure of cases and controls to bowel cancer screening (percentages)**

%	Cases Screened	Cases Not Screened	Total
Controls - Screened	39	20	59
Controls - Not screened	16	25	41
Total	55	45	100

Missing data for tumour pathology variables can be close to 30% with more advanced tumours more likely to have missing pathology data. In a recent retrospective observational study which used NCDR data, Dukes’ staging was available for 75% of the tumours registered between July 2006 and December 2008, however this percentage is likely to increase as time goes on ([name], personal communication).

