Ninety percent of symptomatic CRC cases have been shown to be of Duke's stage B or worse [27], but a proportion of 80% at pathological stage B or worse would be a conservative estimate. Thus, only 56% (0.70 [missingness] × 0.80 [stage B+]) of the registered CRC cases will qualify for the study, and we will therefore inflate the sample size to select N cases so that 0.56*N = 719, i.e. around 1,300 cases.

As we require information regarding disease stage and other tumour attributes to select the cases a posteriori, we are planning to collect pilot data from at least 2,000 cases and twice that number of controls as a further failsafe measure. In addition to providing ample power for an odds ratio of 0.8 overall, this will also (1) provide tighter confidence intervals therefore impacting on significance, (2) confer the same power for an odds ratio of 0.7 in a subgroup comprising half the study population (for example in males, females or a particular subsite), and (3) allow for the investigation of the effect of different screening intervals. It is not clear what we should expect in subgroup analyses, but the observed results in the pilot will guide us in terms of the main study.

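### Admitting only cases with a recorded Dukes' B+ stage can pull the primary odds ratio towards 1 if staging completeness differs by screening status, and the 56% yield ignores the stated link between stage and missingness

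*Protocol article*

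**What the plan says.** In the Protocol article, the subsection on matched general population controls says that in the initial stages "incident cases will be restricted to those individuals with Duke’s stage B or worse primary CRC" (Designs 1-3 of Table 1). The Power calculation section confirms that a recorded stage is a condition of entry: "As we require information regarding disease stage and other tumour attributes to select the cases a posteriori", more pilot cases are to be collected than the calculation requires.

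The same section describes the missing data: "Missing data for tumour pathology variables can be close to 30% with more advanced tumours more likely to have missing pathology data". It adds that in an earlier study "staging was available for 75% of the tumours registered between July 2006 and December 2008", and expects this to improve. On the share of advanced disease it says that "a proportion of 80% at pathological stage B or worse would be a conservative estimate". It then concludes that "only 56% (0.70 [missingness] × 0.80 [stage B+]) of the registered CRC cases will qualify for the study", and inflates 719 cases to around 1,300, with a planned pilot of at least 2,000.

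Data sources & collection takes Dukes' stage from the national repository (NCDR), then adds: "Detailed pathology information is also available via the NHS BCSP".

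Bias & effect modification deals with exposure-opportunity bias and self-selection bias. It does not mention selection through missing stage.

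**The concern.** The primary objective compares screening exposure between B+ cases and their matched controls. A B+ case without a recorded stage never enters that comparison, and its controls leave with it. If the chance of being staged is the same for screened and unscreened B+ cases, only precision is lost. If it differs, the exposure distribution of the analysed cases is distorted and the odds ratio is wrong by a fixed factor at any sample size, including in the national phase.

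There are two routes to such a difference:

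- **Through stage.** The protocol says advanced tumours are more often unstaged. If unscreened B+ cases sit later within B-D than screened ones, they are lost more often. The Background reports stage shifts with screening, so this is plausible. That the shift also holds within B+ is an inference.
- **Through detection mode.** Tumours found by the programme may have a further route to pathology data. The document allows this but does not show it.

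Both routes make screening look less effective than it is. Separately, multiplying 0.70 by 0.80 is valid only if missingness does not depend on stage, which the same section denies.

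**Working it through.** **Inputs from the Power calculation section.** 70% staged (or 75% in the earlier study); 80% B+; 55% of cases screened; 16% of pairs with only the case screened and 20% with only the control screened; 719 cases needed; 2,000 planned. Staging completeness by screening status and the screen-detected share of cases are not given, so every value for them below is an assumption.

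**1. The plan's own figures.** Matched odds ratio = 16/20 = 0.80. Inflation = 719/(0.70 × 0.80) = 719/0.56 = 1,284, which agrees with around 1,300.

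**2. Effect of unequal completeness.** Let s1 and s0 be the proportions staged among screened and unscreened B+ cases. The discordant pairs become 16·s1 and 20·s0, so

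observed OR = 0.80 × s1/s0, with 0.55·s1 + 0.45·s0 = 0.70.

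Overall completeness stands in here for completeness among B+ cases.

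| s1/s0 | s1 | s0 | Gap (points) | Observed OR | Log effect lost |
|---|---|---|---|---|---|
| 1.00 | 70.0% | 70.0% | 0 | 0.80 | 0% |
| 1.118 | 73.5% | 65.7% | 7.8 | 0.894 | 50% |
| 1.25 | 76.9% | 61.5% | 15.4 | 1.00 | 100% |

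With 75% staged overall, the gaps that lose half and all of the effect are 8.3 and 16.5 points. The number of cases does not appear in the formula.

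**3. Stage route alone (assumed inputs).** Take stage missing in 20% of B/C and 60% of D tumours, with D making up 30% of unscreened and 20% of screened B+ cases.

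- s0 = 0.70 × 0.80 + 0.30 × 0.40 = 0.68
- s1 = 0.80 × 0.80 + 0.20 × 0.40 = 0.72
- OR = 0.80 × 0.72/0.68 = 0.847, which is 26% of the log effect lost

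Varying missingness in D over 40-80%, the D share over 25-30% in unscreened cases and over 10-20% in screened cases gives 0.81 to 0.955. More than half the effect is lost only at the most extreme settings.

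**4. Detection-mode route (assumed inputs).** Take 20% of advanced cases screen-detected and 10% of those unstaged. The rest are then unstaged in (0.30 − 0.20 × 0.10)/0.80 = 35%.

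- s1 = (20 × 0.90 + 35 × 0.65)/55 = 40.75/55 = 74.1%
- s0 = 65.0%
- OR = 0.80 × 0.741/0.650 = 0.91, about 59% of the log effect lost

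For 10-30% screen-detected and 5-20% unstaged among them, the range is 0.82 to 1.06. If completeness is equal across detection modes, this route contributes nothing.

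**5. Yield.** With 34% missing in B+ and 14% in A (assumed), overall missingness is 0.80 × 0.34 + 0.20 × 0.14 = 0.30, as stated. The yield is 0.80 × 0.66 = 52.8%, so 2,000 cases give 1,056 instead of 1,120. If all missing stage falls in B+ tumours, missingness there is 0.30/0.80 = 37.5% and the yield is 0.80 × 0.625 = 50%: 1,000 of 2,000, or 719/0.50 = 1,438 cases needed instead of 1,284.

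The figure of 719 is taken as stated. The discordant-pair count behind it is a separate question.

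**The case against.** **Better staging of screen-detected tumours is not shown.** A reader might infer from the sentence on programme pathology that these tumours are better staged. The documents do not support that as fact. Dukes' stage is taken from the NCDR for all cases, nothing says programme data will fill gaps in it, and no completeness by detection mode is given. This objection stands, so that route can only be called possible.

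**The effect need not be large.** A reader might also conclude that most of the planned effect is cancelled. That needs gaps well above 7.8 points, and much of the assumed range loses less than half. Comparing the crude exposures makes the loss look larger: 55% against 59% is an unmatched odds ratio of 0.85, and the example in step 4 moves it to 0.97. The planned effect is the matched 0.80, which moves to 0.91.

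**Other analyses are less exposed.** Design 4 and the secondary objective do not depend on stage, and the analysis of screen-detected cases only cannot be distorted by differences between detection modes. This is true, but neither is the primary comparison. Adjusting for screen-detection in Designs 1 and 2 does not bring back dropped cases.

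**An opposite bias exists.** The protocol discusses missed metastases in screen-detected tumours, which biases in favour of screening. The net direction of all stage-related errors is therefore uncertain, though one bias is not a remedy for another.

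**Missing-data methods may be in an analysis plan that is not shown.** That is so, and the absence of imputation is not the point here. The point rests on the stated entry rule and on the product 0.70 × 0.80.

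**The yield error is small.** This stands: 1,056, or even 1,000, still exceeds the stated 719.

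**Conclusion.** The concern holds in conditional form. The protocol fixes a rule that drops unstaged cases, says that missingness depends on stage, and treats the consequence only as lost numbers. If unscreened B+ cases are staged less completely than screened ones, the primary odds ratio is biased towards 1 and no increase in sample size corrects it.

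A gap of 7.8 points would halve the planned log effect and one of 15.4 points would remove it, given 70% staged, 55% of cases screened, a true matched odds ratio of 0.80, and overall completeness standing in for that among B+ cases. Equal completeness gives no bias. The documents do not say where in this range the study lies, so no single figure for the loss can be claimed.

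The 56% yield contradicts the protocol's own statement about missingness and should be restated. On its own this is minor.

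**What to change.** - Keep unstaged cases and their two controls in the analysis dataset. They are retrieved anyway, because stage is applied after collection.
- Report staging completeness by screening status and by detection mode. This shows directly whether the bias can arise.
- State one stage-source rule and apply it equally to screen-detected and symptomatic cases.
- Alongside the complete-case analysis, add multiple imputation of stage (A versus B+) from detection mode, screening history, subsite, tumour size, treatment, death, age, sex and IMD, all covered by Table 2.
- Add an analysis counting all unstaged cases as B+, and bounds in which the B+ share of unstaged cases differs between screened and unscreened. Counting all unstaged cases as A adds nothing, since it reproduces the complete-case result.
- Restate the yield with missingness depending on stage, for example as a range from 50% to 56%.

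The cost is some extra analysis work. Imputation assumes that stage is missing at random given its predictors, and some predictors, such as tumour size, may be missing together with stage. That is why the bounds should accompany it.

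### At the protocol's own 56% yield, the pilot has about 83% power, not 90%, for an odds ratio of 0.7 in half the study population (two-sided 5%, two controls per case)

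*Protocol article*

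**What the plan says.** All of this is in the Power calculation section of the protocol article.

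- **Target.** "We will therefore assume an odds ratio of 0.8". The power sought is 90%, and the protocol states that this "would require 259 discordant pairs and therefore 719 cases with one control per case". No alpha or sidedness is given.
- **Discordance.** "We anticipate 64% agreement of exposure for matched cases and controls", so 36% of case-control pairs are discordant. Control exposure is put at 59%.
- **Yield.** After allowing for missing staging (0.70) and stage B or worse (0.80), only 56% "of the registered CRC cases will qualify for the study". The protocol uses this to inflate 719 cases to about 1,300.
- **Pilot size.** "we are planning to collect pilot data from at least 2,000 cases and twice that number of controls". This is said to give ample power for an odds ratio of 0.8 overall and also to "confer the same power for an odds ratio of 0.7 in a subgroup comprising half the study population". No calculation is shown for the subgroup statement, and the text does not say whether the 56% was applied to it.
- **Sex split.** National 2010 cases are given as "18,590 male and 14,628 female cases", 33,218 in all.

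Study design & objectives fixes two controls per case.

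**The concern.** The subgroup statement is tied to the 2,000 collected cases, yet the preceding paragraph says that only a little over half of collected cases can be used. If the 56% is carried through, the subgroup is 560 cases rather than 1,000, and the stated power may not follow.

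Statistical methods plans analyses stratified by sex and anatomical subsite. The Power calculation section says that the pilot results will guide the main study, and the Abstract says that results by sex and subsite may point to sex-specific recommendations. A reader weighing a non-significant pilot result in women against a stated 90% power would allow for a 10% chance of missing an odds ratio of 0.7. At 78% power that chance is about 22%.

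**Working it through.** **Inputs from the protocol:** 36% discordant pairs; 56% yield; 2,000 collected cases; two controls per case; odds ratio 0.7; female share 14,628/33,218 = 44.0%.

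**Assumptions:** two-sided 5%; the 36% discordance also holds at an odds ratio of 0.7; the national 2010 sex split applies to the pilot region's qualifying cases.

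**Formula.** With p = OR/(1+OR), the discordant pairs D needed for a given power are

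D = [z(1−α/2)/2 + z(power)·√(p(1−p))]² / (p − 0.5)²

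and, for a given D,

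power = Φ{[√D·|p − 0.5| − z(1−α/2)/2] / √(p(1−p))}.

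Cases with one control each = D/0.36. A second control multiplies the discordant information by 2M/(M+1) = 4/3 for M = 2, so cases = D/0.48.

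**The plan's own figure.** At odds ratio 0.8, 90% power and two-sided 5%, D = 847, not 259. The formula returns 258.5 at an odds ratio of 2/3 (p = 0.40) with two-sided 5% and 90% power. The 259 therefore points to a two-sided 5% test, which is why that alpha is used here. The subgroup statement has no calculation to reproduce.

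**Requirement at odds ratio 0.7.** p = 0.7/1.7 = 0.4118, so |p − 0.5| = 0.0882 and √(p(1−p)) = 0.4922.

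D = (1.96 × 0.5 + 1.2816 × 0.4922)² / 0.0882² = 333.

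This is 333/0.36 ≈ 926 cases with one control each, or 333/0.48 ≈ 694 with two.

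**Power delivered at odds ratio 0.7.** Qualifying cases: 2,000 × 0.56 = 1,120. Half is 560; women 1,120 × 0.440 ≈ 493; men ≈ 627.

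| Subgroup | Cases | One control | Two controls |
|---|---|---|---|
| Half of qualifying | 560 | 71% | 83% |
| Women | 493 | 65% | 78% |
| Men | 627 | 76% | 87% |
| Half, if all 2,000 qualified | 1,000 | 92% | 97% |

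For half with two controls: D = 560 × 0.48 = 268.8; (16.395 × 0.08824 − 0.98)/0.4922 = 0.948; Φ = 0.83.

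**Checks on the second control.** Simulating 1:2 matched sets with 59% control exposure and 36% discordance (conditional score test, 8,000 runs) gave 82.6% for 560 cases and 78.3% for 493. The Dupont matched case-control formula is more favourable: about 86% for half, 81–82% for women and about 90% for men.

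**What 90% would take, with two controls.**
- Yield: 694/1,000 ≈ 69%. By Dupont, 630–639 cases, or about 63–64%.
- Collected cases at 56% yield: 2 × 694/0.56 ≈ 2,480.
- Effect detectable at 56% yield: odds ratio about 0.67 in half and about 0.65 in women.

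**Sensitivity.**
- Yield 0.75 × 0.90 = 67.5%, the more favourable figures in the same section: 675 cases in half, power 89%.
- One-sided 5%, 56% yield, two controls: about 90% in half and 86% in women.

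**Overall claim on the same basis.** Odds ratio 0.8, 1,120 cases, two controls: D = 537.6 and power about 73% (simulation 74%, Dupont 77%).

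**The case against.** **The 56% is cautious.** The protocol calls 80% at stage B or worse conservative, against 90% in symptomatic cases. It reports 75% staging completeness for 2006–2008 and expects improvement, while the pilot uses 2012–2013 diagnoses; and 2,000 is a minimum. This stands as a reason to show a range: at 67.5% yield the gap nearly closes (89%), and under the Dupont formula it closes. But 56% is the yield the protocol itself adopts when it inflates the sample, and the subgroup sentence names no other.

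**The 90% may not be what is meant.** The phrase about the same power could refer back to the overall power for an odds ratio of 0.8. As a pure comparison that is true, since 83% in half exceeds 73% overall. It does not rescue the sentence: the description of overall power as ample rests on the 90% calculation, and 73% does not meet it.

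**The sex figures are approximate.** They apply a national all-case split to one region's stage B or worse cases aged 60–89. This stands, so the figure for half is the main result and the sex figures are illustrative.

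**The larger error is the 259 pairs.** Agreed; that is a separate matter. Correcting it would not correct this statement, because the 333 pairs for an odds ratio of 0.7 are derived without it.

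**Stronger readings to avoid.** A reader might infer that the claim holds only if all 2,000 cases are analysable. That is close to true with one control per case (926 of 1,000, about 93% yield), but the plan has two controls, where about 69% suffices and full yield gives about 97%. Setting the 202 one-to-one pairs from 560 cases (560 × 0.36) against 333 ignores the second control. Nor do the documents say that non-significant pilot subgroup results will be taken as negative: they describe subgroup expectations as unclear and expect power not to be an issue in the main phase.

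**Conclusion.** The concern holds in a limited form. At the protocol's 56% yield, two-sided 5%, 36% discordance and two controls per case, power for an odds ratio of 0.7 is about 83% in half the qualifying cases (about 86% by Dupont), a shortfall of roughly 4 to 7 points from 90%. In women the shortfall is larger (about 78%, or 81–82% by Dupont). In men it is small (about 87%), and by Dupont there is essentially none.

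For a subgroup of half, the shortfall disappears with a one-sided 5% test or a yield near 69%, so the conclusion rests on the unstated alpha being two-sided, which the 259 supports, and on the protocol's stated yield. It concerns secondary analyses in the pilot. It does not show that the pilot is unfit for them, only that the stated power does not follow from the protocol's own inputs.

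**What to change.** Restate the subgroup claim on the qualifying cases, naming alpha, matching ratio and yield. For example: with 1,120 qualifying cases (56% of 2,000), two controls per case and a two-sided 5% test, the pilot has about 83% power for an odds ratio of 0.7 in a subgroup of half (about 78% in women and 87% in men on the national split). Equivalently, it has 90% power at an odds ratio of about 0.67 in half and 0.65 in women. Add that subsites with fewer than half of the cases have less power, and give the figure at a more favourable yield (89% at 67.5%).

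In the same edit, restate the overall claim for an odds ratio of 0.8 on this basis (about 73%), so that the two statements agree. If 90% in half is to be kept at 56% yield, the alternative is to collect about 2,480 cases.

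Rewording costs a sentence or two and makes the stated figures less favourable. It changes nothing in the design.
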